#### Statistical Methods

The statistical analysis of study results will be performed according to the CPMP guidelines for “Biostatistical methodology in clinical trials in applications for marketing authorizations for medicinal products” and the ICH guideline “Statistical principles for clinical trials”.

For all data collected during the trial and reported in the case report forms describing the sample, listings of the individual raw data as well as tables of sample characteristics and/or frequencies will first be given. Continuous data will be summarized first by treatment group, secondly by certain study time points, thirdly by each study centers using descriptive statistics (mean, median, standard deviation [SD], minimum and maximum, number of available observations and number of missing observations). It will be done for absolute and percent changes from baseline too.

Categorical data will be summarized first by treatment group, secondly by certain study time points, thirdly by each study centers. The numbers and percentages of each of categories, the number of available observations and the number of missing observations will be presented in frequency tables.

The trial will be conducted at seven study sites. Therefore centers will be considered as possible prognostic factor influencing the outcome.

With regard to possible baseline and study site effects, the two-sided hypothesis for the continuous primary efficacy variable LVEF at 6 months postoperatively (comp. section 6.1.1) will be assessed using analysis of covariance (ANOVA) at adjusting for baseline LVEF and study site at a 5% level of significance.

Secondary efficacy variables (comp. section 6.1., 6.2.) will be analyzed in a strictly explorative way. If p-values are computed, no adjustment for multiple testing will be made and they will be interpreted in the exploratory sense. Similarly, confidence intervals will be computed. In order to check differences between the treatment groups for the fifth secondary endpoint (death, myocardial infarction, need for reintervention) an unadjusted survival analysis with Kaplan-Meier-estimations will be performed using the log rank test.

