Based on the existing experience, it seems to be justified to conclude that transplantation of purified CD133+ autologous bone marrow cells in the infarct border zone can be safely performed in patients with ischemic heart disease. Neoangiogenesis, neomyogenesis, or both have not been found in humans at this point. With this carefully designed randomized controlled study we will determine the efficacy of clinical cell transplantation for ischemic heart disease. It will be shown whether relevant myocardial regeneration can be induced by using primary isolated CD133+ adult stem/progenitor cells that have not been expanded and modified ex vivo.

On the basis of the demonstration of clinical safety and efficacy in phase I and phase II studies, this study will show the therapeutic effect of CD133+ isolated bone marrow stem cell injection into the myocardium of post infarct patients undergoing coronary artery bypass graft (CABG) operation. Safety and efficacy of the treatment will be clarified in a randomized placebo controlled multicenter study.

So the aim of this clinical trial is to investigate whether injection of autologously derived bone marrow stem cells yields a functional benefit in addition to the CABG operation. The following hypothesis will be tested: "Patients who undergo CABG & stem cell injection have no different left ventricular ejection fraction than patients, who undergo CABG alone, measured by Cardio MRI prior and 6 months after the operation." This will be the primary endpoint. The changes in physical exercise capacity and myocardial perfusion will be assessed by 6 minute walk test, echocardiography, New York Heart Association (NYHA) and Canadian Cardiovascular Society (CCS) status. Patients will also be asked to complete Quality of Life (Minnesota and SF 36) questionnaires. Safety will be assessed by adverse events, the combined clinical endpoints of major adverse cardiac events (MACE: death, recurrent AMI, hospitalization with heart failure or ventricular tachycardia, target vessel revascularization including adverse events and ventricular arrhythmia), laboratory assessments and unwanted tissue changes.

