#### Secondary endpoints

1. Change in LVEF at 6 months post-OP compared with preoperatively (screening) and early postoperatively (discharge) as assessed by MRI and echocardiography.
2. Change in LV dimensions (left ventricular end systolic dimension [LVESD], left ventricular end diastolic dimension [LVEDD]) at 6 month post-OP compared with preoperatively (screening) and early postoperatively (discharge) as assessed by echocardiography.
3. Change in physical exercise capacity determined by 6 minute walk test at 6 months post-OP compared with preoperatively (screening) and early postoperatively (discharge).
4. Change in NYHA and CCS class at 6 months post-OP compared with preoperatively (screening) and early postoperatively (discharge).
5. MACE (cardiac death, myocardial infarction, secondary intervention/reoperation, ventricular arrhythmia).
6. QoL-score at 6 months post-OP compared with preoperatively (screening) and 3 months post-OP (telephone).

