#### *6.3.1.6 Major Adverse Cardiovascular Events – MACE*

Major adverse cardiovascular events patient alive no/yes, reoperation no/yes, secondary ICU admission no/yes, infarction post-OP no/yes, readmission no/yes, reintervention no/yes, new ventricular arrhythmia no/yes) will be separately assessed at Assessment V (6 months after OP) and 24-Month Follow-Up.

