### **8.5 Efficacy Analyses**

The trial will be conducted in seven study sites. Therefore centers will be considered as possible prognostic factor influencing the outcome.

With regard to possible baseline and study site effects, the two-sided hypothesis for the continuous primary efficacy variable LVEF at 6 months postoperatively (comp. section 6.1.1) will be assessed using analysis of covariance (ANCOVA) adjusting for baseline LVEF and study sites.

Secondary efficacy variables (comp. section 6.1.1) will be analyzed in a strictly explorative way. The distance walked pre-op and post-op will be compared. If p-values are computed, no adjustment for multiple testing will be made and they will be interpreted in the exploratory sense. Similarly, confidence intervals computed will be interpreted as interval estimates for presence or absence of effects in the study data.

In order to check differences between the treatment groups for the fifth secondary endpoint (death, myocardial infarction, need of reintervention) an unadjusted survival analysis with Kaplan-Meier estimations will be performed using the logrank test.

Details of the statistical analyses will be documented in SAP (Statistical Analysis Plan) that is to finalize before unblinding.

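### The log-rank test of the fifth secondary endpoint uses a different composite from the MACE endpoint listed under that number: it omits ventricular arrhythmia and replaces cardiac death with death

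*Protocol*

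**What the plan says.** **Endpoint lists.** The synopsis and section 3.2 both give the fifth secondary endpoint as "MACE (cardiac death, myocardial infarction, secondary intervention/reoperation, ventricular arrhythmia". Section 8.8 repeats these four components as the interim safety item. The synopsis safety parameters do too, with a supraventricular tachyarrhythmia item placed beside them.

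**Analysis text.** Section 8.5 plans, "for the fifth secondary endpoint (death, myocardial infarction, need of reintervention) an unadjusted survival analysis", using Kaplan-Meier estimates and the log-rank test. The synopsis has the same rule: "fifth secondary endpoint (death, myocardial infarction, need for reintervention) an unadjusted survival analysis".

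**Rationale.** Section 1.2 describes the combined safety endpoint as "MACE: death, recurrent AMI, hospitalization with heart failure or ventricular tachycardia, target vessel revascularization including adverse events and ventricular arrhythmia".

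**Collection.** Section 6.3.1.6 records MACE as separate items at 6 and 24 months, starting with "patient alive no/yes" and continuing "reoperation no/yes, secondary ICU admission no/yes, infarction post-OP no/yes, readmission no/yes, reintervention no/yes, new ventricular arrhythmia no/yes". The MACE safety tables in section 8.6 refer to this section, not to the endpoint list.

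**Status.** Section 8.5 treats all secondary efficacy variables as exploratory, without adjustment for multiple testing.

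**The concern.** Section 8.5 identifies the tested endpoint by its number and then describes something else. An analyst who follows the wording in brackets does not test the endpoint that was listed. An analyst who follows the number departs from the written analysis. Both readings can be defended from the protocol, and they count different patients.

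The component that drops out is not a neutral one. Ventricular arrhythmia is among the potential risks of cardiac stem cell therapy in section 1.3, and it appears in every list that carries the MACE label. It is missing only from the list that is tested between the arms over time. At stake is whether the report's one time-to-event comparison of major cardiac events answers the question set in section 3.2.

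**Working it through.** The protocol states no event count, event rate, hazard ratio or power for this comparison, so there is no figure to reproduce. The check is a comparison of the component lists.

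| Component | Endpoint list (synopsis, 3.2) and 8.8 | Log-rank text (synopsis, 8.5) | Rationale (1.2) | Items collected (6.3.1.6) |
|---|---|---|---|---|
| Death | cardiac only | death, cause not restricted | death, cause not restricted | vital status |
| Infarction | yes | yes | recurrent acute | postoperative |
| Repeat procedure | intervention or reoperation | reintervention; reoperation not named | target vessel only | reoperation and reintervention, separately |
| Ventricular arrhythmia | yes | **absent** | yes | new arrhythmia |
| Other | none | none | hospital stay for heart failure or ventricular tachycardia | secondary ICU admission; readmission |

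1. **Is it a numbering slip?** No. In both endpoint lists item 4 is NYHA and CCS class, item 5 is MACE and item 6 is quality of life. Item 5 is the only one of the six that is a composite of clinical events.

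2. **How many lists are there?** There are four distinct component sets. Three carry the MACE label. The fourth, in the log-rank text, is tied to MACE only through the words naming it the fifth secondary endpoint.

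3. **What does the difference do to individual patients?**
   - A patient whose only event is a ventricular arrhythmia has an event under 3.2 and 8.8, but is event-free in the log-rank.
   - A patient who dies of a non-cardiac cause, with no other event, has an event in the log-rank but not under 3.2.
   - A patient with a reoperation has an event under 3.2. Under 8.5 it depends on whether reintervention is meant to include reoperation.
   - A patient whose only event is a readmission is flagged on the collection items, but has no event under 3.2 or 8.5.

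4. **Is there a rule of precedence?** None of these sections says which list governs.

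5. **Scale, on an assumption.** The only six-month composite rate in the document is 9.9% (section 1.3). It is a MACCE rate from a different bypass cohort, includes cerebrovascular events, and the protocol says the rate here might be higher. With expected events = patients × rate, and a rate assumed between 5% and 25%:
   - 142 × 0.05 = 7.1
   - 142 × 0.099 = 14.1
   - 142 × 0.25 = 35.5

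   That is about 7 to 36 events over both arms. With so few, reclassifying a handful of patients can visibly change the curves. How many would be reclassified cannot be derived, because no rate is given for any single component.

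**The case against.** The strongest case against is that this is one bracketed phrase in an exploratory analysis. The listed endpoint is the same in the synopsis, 3.2 and 8.8. Section 1.2 is background prose. Section 6.3.1.6 is a set of yes/no items with no rule that each counts towards a composite. All of that is fair. The operative conflict is between the endpoint list and the analysis text; the other two lists matter because nothing ranks them and because the safety tables draw on 6.3.1.6.

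Several stronger readings are tempting but are not supported.

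- **That the interim safety review is compromised.** A reader might infer this because MACE is its only item. Section 8.8 repeats the 3.2 components, ventricular arrhythmia included, so it does not conflict with the endpoint list.
- **That the planned Kaplan-Meier censors non-cardiac deaths.** As worded, 8.5 counts death without restriction, so those deaths are events. Censoring would arise only if the cardiac-death wording of 3.2 were carried into the analysis. The tested composite does not itself mix two definitions of death.
- **That the definition will be picked after seeing results.** Section 8 requires the SAP to be final before unblinding. The SAP is not at hand, so selection by outcome is not shown. Even so, a SAP that follows one of these sections must depart from the other.
- **That arrhythmia data are lost.** They are not. Ventricular arrhythmia is a collected MACE item, an adverse event of specific interest (Appendix 2), part of the interim item, and assessed by Holter. Only the log-rank omits it.
- **That a stated share of events would move.** This needs a component rate that the protocol does not give, and adding component rates overstates the change because a first-event analysis counts each patient once.
- **That the log-rank should be stratified by site.** The protocol expressly chose an unadjusted analysis, and this contradiction gives no reason to revisit that choice.

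**Conclusion.** The point stands as a contradiction within the protocol. The log-rank is described as testing the fifth secondary endpoint, but the composite it spells out differs from that endpoint in at least two respects: ventricular arrhythmia is absent, and death replaces cardiac death. Whether reoperation counts is unclear. It is not a detail left to the SAP, because the synopsis and the body each state both versions.

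The consequence is limited. The comparison is exploratory, so the confirmatory test of LVEF, its alpha and the sample size are untouched. The effect on the result cannot be quantified from the document. The 7 to 36 events are an assumed scale, not a prediction. The conclusion rests on the wording alone and needs no assumed rate. It is worth correcting because the omitted component is a named risk and the correction is cheap.

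**What to change.** State one component list, including ventricular arrhythmia and one explicit definition of death, in the synopsis and in sections 1.2, 3.2, 8.5 and 8.8. Run the Kaplan-Meier estimates and the log-rank test on exactly that composite.

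All-cause death is the simpler choice: 8.5 already says death, 6.3.1.6 already records vital status, and it avoids censoring non-cardiac deaths. Say whether reintervention includes reoperation.

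In 6.3.1.6, mark which items count towards the composite, so that the safety tables in 8.6 and the log-rank use the same events. Report readmission and secondary ICU admission separately.

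**Cost.** No new data collection is needed: the components are on the MACE items, with death as vital status, and section 6.3.1.3.1 records onset dates for adverse events. It is nevertheless more than an edit of wording. With all-cause death the listed secondary endpoint changes slightly, because a few non-cardiac deaths may enter. Arrhythmia found only on a scheduled Holter (discharge, 6 months) has an approximate onset date, since it is known only to have appeared by that recording; the dating convention should be written down beforehand.

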#### 4.5 Patient Identification and Randomization

Upon enrollment, each patient will receive a four-digit **patient number** consisting of (x-yza). The 1st digit assigned x, indicates the study site (–see List of trial personnel), the 2nd, 3rd and 4th digit assigned, yza, indicates the individual patient. Enrolled patients who drop out of the study before randomization will retain their patient number.

Randomization to study treatment will occur at Assessment Ia (cell-preparation) after all screening procedures have been performed, eligibility for the study confirmed and after bone-marrow aspiration. The randomization will be attributed by Team A (cell processing team). Each randomized patient will receive a four-digit **randomization number** (x-yza). The 1st digit assigned, x, indicates the study site (–see List of trial personnel), the 2nd and 3rd and 4th digit assigned, yza, indicates the individual patient.

Randomized patients who terminate their study participation for any reason, regardless of whether study intervention was taken or not, will retain their randomization number. The randomization code will be assigned using sealed envelopes provided to the Team A for each study center.

Patients will be randomized on a 1:1 basis to receive CD133+ cells or placebo.

The randomization procedure will be stratified by study site and a sequence of randomization numbers will be assigned to the bone-marrow isolation laboratory (Team A) preparing for the study centers. As randomization procedure the Permuted Block Design within strata will be used (Rosenberger and Lachin, 2002). The block size within each stratum will be randomly selected. The size of the randomization blocks as well as seed numbers will be documented but will not be disclosed to the study centers to avoid predictability of treatment. The study treatment will be randomly assigned to the randomization numbers in advance according to the randomization list held by the Biostatistician.

The randomization envelopes are numbered in an ascending order. If a patient is going to be randomized a member of Team A opens the envelope with the lowest number among all unused sealed envelopes available for this center. According to the information randomization will be carried out and CD133+ cell or placebo product will be produced for the current patient.

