## 8.2 **General Considerations**

In statistical analyses no missing values will be replaced.

All statistical analyses are performed by the Institute of Medical Informatics and Biometry of the University of Rostock. Statistical analyses will be carried out using the SPSS statistical analysis system, version 14.0.

All statistical tests will be conducted using a two-sided test with  $\alpha=0.05$ , unless otherwise stated.

For all data collected during the trial and reported in the CRF describing the sample, listings of the individual raw data as well as tables of sample characteristics and/or frequencies will first be given. Continuous data will be summarized first by treatment group, secondly by certain study time points, thirdly by each study center using descriptive statistics (mean, median, standard deviation [SD], minimum and maximum, number of available observations and number of missing observations). It will be done for absolute and percent changes and if appropriate from baseline screening too.

Categorical data will be summarized first by treatment group, secondly by certain study time points, thirdly by each study centers. The numbers and percentages of each of categories, the number of available observations and the number of missing observations will be presented in frequency tables.

Any outliers that are detected during the blind review of the data will be investigated. Methods for dealing with outliers will be defined in the SAP or in an addendum to the SAP, prior to unblinding.

The statistical analysis of study results will be performed according to the CPMP guidelines for “Biostatistical methodology in clinical trials in applications for marketing authorizations for medicinal products” and the ICH guideline “Statistical principles for clinical trials”.

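### The exploratory MACE log-rank test ignores the site stratification used in randomisation; a site-stratified test costs essentially nothing and gains a little power when sites differ

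*Protocol*

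**What the plan says.** Protocol section 4.5: "The randomization procedure will be stratified by study site", using permuted blocks within each site and 1:1 allocation.

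Protocol section 8.5 opens by stating that "centers will be considered as possible prognostic factor influencing the outcome". The primary endpoint is then assessed by "analysis of covariance (ANCOVA) adjusting for baseline LVEF and study sites".

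For the fifth secondary endpoint, the same section specifies that "an unadjusted survival analysis with Kaplan-Meier estimations will be performed using the logrank test". The Statistical Methods part of the synopsis says the same. Secondary efficacy variables as a whole "will be analyzed in a strictly explorative way", without multiplicity adjustment.

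The protocol leaves further detail to a statistical analysis plan that is not available here. The word unadjusted, however, is fixed in the protocol itself.

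**The concern.** Balancing arms within each site removes between-site variation from the treatment comparison. An analysis that ignores site still counts that variation in its variance. If sites differ in event risk, the unadjusted test therefore rejects too rarely under the null and loses some power under an alternative.

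Site differences are plausible in this trial because section 5.2 leaves the cardioplegia technique, and patient treatment generally, to centre standards. At stake is a modest loss of precision in one exploratory comparison, with an analysis that matches neither the randomisation nor the primary model.

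**Working it through.** **The plan's own figure.** The protocol states no event count or power for MACE. Its sample size for LVEF (section 8.7) reproduces: difference 4.5, SD 7.5 and two-sided 5% give 60 per group by the non-central t (power 90.3%). Allowing for 15% drop-out, 120 / 0.85 = 141.2, rounded up to 142.

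**Inputs from the protocol**
- 142 patients at seven centres, 20 to 80 per centre (section 4.4). Since 7 x 20 = 140, keeping to the minimum of 20 forces nearly equal sites, for example 22 + 6 x 20.
- 1:1 permuted blocks within site (4.5); two-sided 5% (8.2); 6 months of follow-up.
- The nearest event rate is 9.9% MACCE at 6 months in an external CABG cohort. Section 1.3 says the trial's rate might be higher. 0.099 x 142 = 14.1 events, about 2 per site.

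**Assumed, because the protocol gives no values**
- Control risk 5%, 9.9%, 20% or 30%.
- Hazard ratio (HR) 0.3, 0.5, 2 or 3.
- SD of the site log-hazard 0, 0.25, 0.5 or 1.0. An SD of 1.0 is a large difference: a site one SD above the mean has exp(2) = 7.4 times the hazard of a site one SD below.

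**Tests compared on the same simulated data**
- Unadjusted: Z = (O - E) / sqrt(V), with E and V computed from the pooled risk sets.
- Stratified: Z = sum over sites of (O_s - E_s), divided by sqrt(sum of V_s), with each site's own risk sets.

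**Power, unadjusted / stratified (%), for 9.9% control risk, N = 142, equal sites, 20,000 to 40,000 trials per scenario**

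| Site SD | HR 0.3 | HR 0.5 | HR 2 | HR 3 |
|---|---|---|---|---|
| 0 | 37.7 / 37.5 | 18.8 / 18.7 | 32.9 / 32.7 | 76.1 / 75.9 |
| 0.5 | 37.1 / 37.5 | 18.4 / 18.8 | 31.4 / 32.6 | 73.1 / 74.3 |
| 1.0 | 35.1 / 37.7 | 16.7 / 19.0 | 26.4 / 31.3 | 64.8 / 70.4 |

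- **Cost.** The largest loss in any scenario was 0.8 points (N = 120, 30% risk, HR 2, no site differences: 66.5% against 65.7%).
- **Size under the null at site SD 1.0.** The unadjusted test had 3.9% at 9.9% risk and 3.0% at 30% risk. The stratified test stayed between 4.7% and 5.2%.

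**Fixed site rates with sites at the planned size (22 + 6 x 20, evenly spaced rates, blocks of 4, 3,000 runs per case)**

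| Site event rates | Case | Unadjusted | Stratified |
|---|---|---|---|
| 5-15% | HR 0.3 | 36.7% | 36.9% |
| 3-25% | HR 0.3 | 50.7% | 52.1% |
| 3-40% | HR 0.3 | 68.5% | 70.6% |
| 3-40% | HR 0.5 | 36.0% | 38.3% |
| 3-40% | null (size) | 4.4% | 5.4% |

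With 3,000 runs, the Monte Carlo standard error of a 5.4% size is sqrt(0.054 x 0.946 / 3000) = 0.4 points, so 5.4% is compatible with 5%.

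**Why sparse events do little harm.** Each event contributes a variance of p(1 - p), where p is one arm's share of the risk set. About 20 patients per site, balanced by blocks, keep p near one half within each site, much as in the pooled risk set. Two events per site therefore lose very little information.

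**The case against.** The strongest counter-case is that nothing here is wrong. An unadjusted log-rank is valid under stratified randomisation and errs only on the conservative side. In section 8.5 the remark about centres leads into the primary LVEF model and does not commit the secondary endpoints to site adjustment. No decision rests on this p-value. A stratified p-value beside unstratified curves also does not test exactly the curves displayed.

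Most of this stands, and it makes the point an improvement rather than an error. It does not remove the point: the choice is fixed without a reason, while the alternative follows the randomisation at almost no cost. Showing Kaplan-Meier curves by arm beside a stratified test is ordinary practice.

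A further objection, that about 14 events over seven sites are too few to stratify, is answered by the simulations.

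A reader might infer that the unadjusted test could hide a real safety difference. The protocol does not support this. Section 8.6 compares adverse events by Fisher's exact test and presents MACE in tables. The stopping rule in section 9.9 uses a chi-square test on class III to V events. At the interim analysis, the synopsis has MACE evaluated descriptively. None of these uses the log-rank.

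**Conclusion.** The point holds as a small, nearly free improvement. The unadjusted test is valid and mildly conservative when sites differ. Stratifying by site costs at most about 0.8 points of power when sites are alike. With sites near their planned size, it gains about 1 point at site rates of 3-25% and about 2 points at 3-40%.

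A reader might take the larger simulated gains as typical. They are not: the maximum of about 14 points needs 30% control risk, HR 2 and a site log-hazard SD of 1.0, and nothing in the protocol indicates site differences of that size.

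Power for MACE is low with either test unless the effect is large. Schoenfeld's formula with 14 events, power = Phi(sqrt(14)/2 x |ln HR| - 1.96), gives 25% at HR 0.5 and 62% at HR 0.3. If 9.9% is the control risk and HR is 0.3, only about 9 events are expected, and simulated power is about 37-38%. The event count limits this comparison far more than the choice of test.

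All of this rests on assumed event rates, hazard ratios and site variation. The event rate also depends on the endpoint definition: section 3.2 lists cardiac death and includes ventricular arrhythmia, whereas section 8.5 lists death, infarction and reintervention. That separate discrepancy needs reconciling.

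**What to change.** In section 8.5 and in the synopsis, specify the log-rank test for the fifth secondary endpoint as stratified by study site. Keep the Kaplan-Meier curves by treatment group. Optionally, report the unadjusted log-rank as a supportive analysis.

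The cost is a few words in two places. It needs no extra data and no change to the sample size, the safety analyses or the stopping rule.
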